### 3.1. Tests

The following psychometric tests, previously used in the STEP IN AMI trial, will be administered to all subjects in all four groups at enrollment and at the one and five-year follow-up: the Self-evaluation test, assessing the global level of psychological distress over the preceding two weeks [46]; the Social Support Questionnaire, evaluating the individual’s perception of his/her social network [47,48]; and the Beck Depression Inventory (BDI), evaluating symptoms of major or minor depression [30,31], where a score between 10 and 15 is considered indicative of mild depression symptoms, and a score equal or higher than 16 indicates clinically significant depression. In addition, the State-Trait Anxiety Inventory (STAI) [49] and State-Trait Anger Expression Inventory (STAXI 2) [50] will also be administered at the same time points.

Quality of life will be evaluated at enrollment and after one and five years in AMI, TTS, BC patients, and HS. In patients with AMI and TTS, the Mac New Heart Disease Health-Related Quality of Life Questionnaire will be utilized to assess three specific domains: emotional, physical, and social, as well as a global QOL score [33].

In women with BC two specific psychometric tests evaluating quality of life have been selected: the EORTC QLQ-C30 (European Organization for Research and Treatment of Cancer Quality of Life- Cancer 30, version 3) [51] and the QLQ-BR23 (Quality of Life Questionnaire for Breast cancer 23) as a supplement for assessing specific quality of life issues relevant to patients with breast cancer [52]. The QLQ-C30 incorporates nine multi-item scales: five functional scales (physical, role, cognitive, emotional, and social); three symptom scales (fatigue, pain, nausea, and vomiting); and a global health and quality of life scale. The QLQ-BR23 consists of 23 items covering symptoms and side effects related to different treatment modalities, body image, sexuality, and future perspective.

In HS the Short Form 36 (SF 36) Health Survey Questionnaire will be administered at enrollment and at the one and five-year follow-up [53,54]. It is a 36 item questionnaire, which measures eight variables: physical functioning, social functioning, role limitation due to physical problems, role limitations due to emotional problems, mental health, energy and vitality, bodily pain, and general perception of health. A single item assesses changes in the respondent’s health over the past year. Final scores range from 0 (worst possible health) to 100 (best possible health). Two summary scores are produced: the Mental Health Component Score (which is the result of mental health, role limitations due to emotional problems, and social functioning scores) and the Physical Component Score (which is the result of physical functioning, role limitation due to physical problems, and pain scores) [55].

At enrollment, two qualitative questionnaires are timetabled for all four groups: (1) the perception of body and emotions (enrollment body perception questionnaire; Supplementary Material S1) (2) the subject’s memory of last week, last month, last year, and past years’ dreams (enrollment dream questionnaire, Supplementary Material S3).

At the one-year follow-up, the 1-year follow-up body perception questionnaire (Supplementary Material S2); and the 1-year follow-up dream questionnaire (Supplementary Material S4) are scheduled for all four groups.

For patients, who have undergone psychotherapy, the oneiric material collected during the training will be reported in the section of last years’ dreams. In particular, these two questionnaires will permit evaluation of qualitative changes during psychotherapy, compared to the control group. These two qualitative questionnaires have been specifically developed for this research. The open questions listed in both have been elaborated based on the observations that emerged from the psychotherapeutic practice in the STEP IN AMI trial. For this reason, they are original and their validity will be tested for the first time.

The enrollment dream questionnaire (Supplementary Material S3) retrospectively explores dream patterns from childhood and adolescence, as specified above.

The 6DT will be administered to all subjects at enrollment and the one-year follow-up.

The 6DT is a projective non-structured test defined by the ontopsychological school allowing for a global view of the subject’s psychological and existential situation. It was used to guide therapy in the STEP-IN-AMI trial [27,28]. In this test, the subject is given six blank sheets of paper on which he/she is asked to draw six pictures in the following order: a tree, a person of the same sex, a person of the other sex, a family, the present situation and the future situation. A detailed description of the test can be found elsewhere [27,28,33].

The 6DT is scheduled to be administered to all subjects at enrollment and the one-year follow-up.

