### 2.3. Therapies

Drug therapy in both the acute and chronic phase of the illness is left to the treating physician’s discretion and recorded in the case report. Psychopharmacological treatment is not part of this protocol but is recorded in the case report form.

Ontopsychological psychotherapy is a humanistic-existential treatment associated with psychodynamic analysis [29]. It is an original and complex synthesis derived from Freudian psychoanalysis, Jungian analytical psychology, and humanistic-existential psychology, as described by Abraham Maslow [40]. Ontopsychological theory considers the human being as a complex system whereby anything that happens in the body may influence the psyche and vice versa. The bidirectional connections between psyche and body may be considered scientifically based on several studies in the field of psycho-neuro-endocrine-immunology [41,42,43]. In this view, a psychotherapeutic intervention must improve global health to be considered efficacious. This approach includes a thorough analysis of unconscious dynamics, mainly represented by body emotions and dream material [29]. Ontopsychology introduces a new vision of the unconscious dimension, that is sustained by a positive nucleus, which has been called *“In-Self”* (In Sé). It characterizes our specific identity, acting through the vital drive that guides human life, and may be considered the criterion of nature, our specific identity which sustains us throughout life. Other fundamental and distinctive concepts of ontopsychology include: a different and more complex characterization of the *SuperEgo* than in psychoanalysis and a great importance given to the communication process, in particular non-verbal communication, represented both by Physiognomy-Kinesics-Proxemics, and the *semantic field* [44]. The semantic field is a concept developed by pioneers of the ontopsychological school. It is a specific aspect of unconscious communication, a complex interplay of psychic and biological data that emanate unconsciously from every person during all interpersonal interactions.

On the basis of its peculiar topographic and dynamic conception of the unconscious, the meaning of symbolic dream images has also been re-codified according to the theory of interpretation [45], with substantial differences compared to Freudian and Jungian psychoanalytic interpretation.

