#### 3.2.2. Treatment Choice, Implementation, and Group Allocation

In the second phase, all pts with TTS, AMI, and BC will be asked to freely choose between ontopsychological STP along with standard medical therapy and, whenever indicated, rehabilitation therapy or medical therapy plus rehabilitation alone.

Therefore, this phase results in seven study groups: three groups of pts (AMI, TTS, and BC) undergoing psychotherapy, three groups of pts (AMI, TTS, and BC) on standard medical therapy, and one group of HS.

There will be four independent areas of research: (1) AMI pts following psychotherapy (AMI-PSY) will be compared with AMI pts, without psychotherapy (AMI-C); (2) TTS pts who will follow psychotherapy (TTS-PSY) will be compared with TTS pts without psychotherapy (TTS-C); (3) BC pts with psychotherapy (BC-PSY), will be compared with BC pts without psychotherapy (BC-C); (4) HS subjects, after the initial comparative evaluation with the other enrolled groups, will have an independent follow-up, where psychological data collected at enrollment will be compared with psychological data collected at one year and with clinical follow-up at five years.

Since the research is observational, it is not possible to foretell how many patients will choose psychotherapy plus medical therapy or standard medical care alone.

If balanced patient groups can be formed, statistical analysis evaluating differences between groups will be performed. Thus, it may be possible to evaluate how psychotherapy may impact the real world because patients will have a choice between psychotherapy plus medical care or medical care alone. It will also be possible to evaluate if psychotherapy might result in an improvement in psychological patterns compared to medical therapy alone, and how this can translate in an improvement in medical prognosis. Moreover, the patients’ choice might provide useful information to improve a more individualized therapy and hospital organization.

AMI-PSY and TTS-PSY patients will be referred to the outpatient clinic of Cardiac Psychology at San Filippo Neri Hospital in Rome; BC-PSY will be referred to the outpatient clinic of Psycho Oncology in the same hospital. Psychotherapy will be provided in individual sessions (maximum of ten) and five group meetings, as in the STEP IN AMI trial. Psychotherapy will be conducted by two expert psychotherapists trained in ontopsychology and psychosomatics.

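### Dreams collected in therapy sessions enter the one-year dream questionnaire for psychotherapy patients only, so its last-year section is not comparable with controls

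*Protocol article*

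**What the plan says.** Section 3.1 (Tests) states that "the 1-year follow-up dream questionnaire (Supplementary Material S4) are scheduled for all four groups", so the instrument is common to everyone. It then adds a rule for one group: "For patients, who have undergone psychotherapy, the oneiric material collected during the training will be reported in the section of last years’ dreams". The sentence after that gives the purpose: "these two questionnaires will permit evaluation of qualitative changes during psychotherapy, compared to the control group".

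Two other places show what the added source is. Section 3.2.2 says: "Psychotherapy will be provided in individual sessions (maximum of ten) and five group meetings". Section 2.3 describes the treatment as including a "thorough analysis of unconscious dynamics, mainly represented by body emotions and dream material". Dreams are therefore central to the therapy, not an incidental by-product.

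Section 2.1 lists dream symbols and patterns at baseline and follow-up among the aims. Section 3 defines the dream variable as what the subject remembers of dreams over stated look-back periods. The rationale for the aims names absent or selective dream memory among the patterns thought to improve with this therapy.

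**The concern.** The same section of the same form is filled in two ways. A patient who declined psychotherapy contributes what he or she recalls when the questionnaire is given. A treated patient contributes that recall plus dreams gathered earlier, close to when they occurred, in sessions where dreams are actively sought.

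Because the variable is defined as memory of dreams, the added material also changes what is measured. A treated patient who recalls nothing at one year can still have a filled section, while an identical untreated patient has an empty one. The distortion runs in the direction of the study's hypothesis.

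Within treated patients there is a related problem. The enrollment questionnaire precedes any session, so its last-year section holds recall only, whereas the one-year section holds recall plus session material. Any apparent gain in that section mixes a change in the patient with a change in how the data were collected.

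**Working it through.** **Which questionnaire is affected.** The sentence on session dreams names no time point. Therapy is chosen and delivered after enrollment (section 3.2.2), and the sentence directly follows the one scheduling the one-year forms. The one-year dream questionnaire is therefore meant.

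**Sources feeding the last-year section, as written.**

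| | Enrollment | One year |
|---|---|---|
| Psychotherapy patients | recall | recall + session dreams |
| Patients without psychotherapy | recall | recall |
| Healthy subjects | recall | recall |

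The only unequal cell is psychotherapy patients at one year. The term control group could mean untreated patients or healthy subjects; neither has study sessions, so the asymmetry exists on both readings. Study contacts at which dreams could be collected number at most 10 + 5 = 15 in treated patients and 0 in the others. The article does not provide parallel collection in controls, keep session dreams apart, or restrict the comparison to visit recall. The external committee and the dream manual in section 4 concern evaluation and classification, and neither equalises collection.

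**Size.** The plan gives no figure to reproduce: there are no dream counts, symbol frequencies or scoring rule. What follows is illustration on stated assumptions, with no true difference between groups.

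*Model 1, counting dreams.* Assume each dream shows a given symbol with probability 0.10, dreams are independent, each person recalls 3 dreams at the visit, and a person is positive if the symbol appears at least once. With n dreams recorded, P(positive) = 1 − 0.9^n.

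- Control, n = 3: 1 − 0.9^3 = 0.271, or 27%.
- Psychotherapy with 5 session dreams, n = 8: 1 − 0.9^8 = 0.570, or 57%; difference about 30 points.
- Psychotherapy with 10 session dreams, n = 13: 1 − 0.9^13 = 0.746, or 75%; difference about 47 points (0.746 − 0.271 = 0.475).

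*Model 2, counting collection occasions.* Assume a pattern is captured with probability q at each independent occasion, with 1 occasion for controls and 1 + k for treated patients. P(captured) = 1 − (1 − q)^(1+k).

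| q | Control | k = 5 | k = 10 | k = 15 |
|---|---|---|---|---|
| 0.05 | 5% | 27% | 43% | 56% |
| 0.10 | 10% | 47% | 69% | 81% |
| 0.20 | 20% | 74% | 91% | 97% |

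Both models give the same direction. The magnitude depends wholly on the assumptions.

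*When the distortion would be absent.* If the measure were instead the share of recorded dreams showing the symbol, the expectation under Model 1 is 10% in both groups (0.3/3 and 1.3/13). Counts, presence-or-absence measures and memory measures are exposed; a per-dream share need not be.

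**After the fix.** With visit answers alone, n = 3 in both groups in Model 1 (27% versus 27%), and there is one occasion each in Model 2. The expected difference with no true effect is zero.

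**The case against.** The strongest reply is that the problem is narrow and its size unknown. Several parts of that reply stand.

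- *Scope.* Session material goes into one section of one questionnaire. The enrollment version also asks about the last week and last month; if the one-year version keeps those windows, they remain comparable. The one-year form is in supplementary material that is not at hand, so it cannot be excluded that its layout marks the source of each dream. A reader might infer that the whole dream comparison is invalid. The text does not support that.
- *Volume.* A reader might infer that everything said in 15 sessions is transferred. The article gives maximum session numbers, but not how many dreams are recorded or whether group meetings yield any.
- *Certainty.* A reader might conclude that a difference is guaranteed. The endpoint is qualitative, section 4 says the features of dream symbols and patterns cannot be foreseen, and no at-least-once rule is stated. A per-dream classification would not produce the gaps shown above.
- *Change from baseline.* A reader might infer that all change in treated patients is inflated. Enrollment reaches back to childhood and adolescence and so has the wider window overall. The distortion applies only when last-year sections are compared like for like.
- *Importance.* The Discussion places the primary purpose at enrollment, between-group testing depends on balanced groups forming, and section 4 calls the research a pilot.

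One might also ask whether those who code the dreams are masked to group. That is a separate matter and does not follow from this defect.

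What the reply does not remove is the plain sequence in section 3.1: an extra source for one group, then a comparison with the group that lacks it. Exploratory status does not help, because an artefact of collection generates false hypotheses as readily as it produces false confirmations.

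**Conclusion.** The point holds in limited form. As written, the last-year dream section at one year is ascertained differently in psychotherapy patients and controls, and the article uses the questionnaires to compare them. The direction is towards more dreams, more symbols or better dream memory with psychotherapy in the absence of any effect. The like-for-like last-year comparison with enrollment in treated patients is affected too.

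No magnitude can be derived from the document. The illustrative 27% against 57% or 75% needs all four assumptions of Model 1: symbol frequency, number of dreams, independence and at-least-once scoring. The figures show that the distortion could be large, not that it is.

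The enrollment comparison, body perception questionnaire, Six Drawing test, psychometric tests and medical endpoints are untouched. For one section of an exploratory instrument this is a should-fix matter, not a threat to the study as a whole.

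**What to change.** State that every psychotherapy-versus-control dream comparison, and every comparison of one year with enrollment, uses only answers elicited at the study visit by the same questionnaire procedure in all groups. Record session dreams in a separate field, identified by source, and use them only to describe the psychotherapy group.

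The cost is one case-report-form field and one sentence in the plan; no session material is lost. It is better done soon: the Enrollment Status paragraph reports that 15 + 5 + 1 = 21 of the 19 + 11 + 4 = 34 patients enrolled so far chose psychotherapy, and dreams already merged without a source label may be hard to separate later. For forms already completed, the source of each entry should be marked where session records allow, and any section that cannot be separated should be left out of the comparison and its number reported.

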Moreover, the encouraging results of the STEP-IN-AMI trial suggest that several specific psychosomatic issues deserve further evaluation in a wider clinical context to assess new potential diagnostic, preventive, and therapeutic strategies which may potentially extend to other diseases. Particularly, the study analysis revealed for the first time two main psychological patterns:(1)Poor awareness of emotions, which may have reflected a lack of the perception of one’s body, or parts of one’s body. Patients seemed to have a painful perception of parts of their body (mainly the head and/or the chest, with particular reference to their heart), whereas they did not have a perception of other parts, as if they were “anesthetized”. In the STEP-IN-AMI pts, there was an improvement of body/emotional perception during psychotherapeutic intervention with body relaxation training [33], conducted both in individual and group meetings. Patients were encouraged to explore their bodily sensations, starting with the visceral zone (i.e., abdomen), with the help of abdominal breathing. From our experience, abdominal breathing seems to act as a strong stimulus to the visceral brain, which is continuously active throughout one’s entire life (even if we have lost our conscious perception of it), and the subjective contact with the visceral zone translates as an important mediator of inner emotions and feelings [34].(2)An apparent presence of specific dream configurations in the period before AMI (i.e., distressing dreams or repeated nightmares; no memory of dream content; or selective memory only of dreams of childhood and adolescence), which again improved when recovering from the acute event in those undergoing STP [10,11].

Following observations from ontopsychology, the dream pattern seems to follow a hierarchical approach [27]. In particular, the unconscious dynamics of the dream seem to primarily aim at the optimal psycho-physical evolution of the dreamer, the basic one being the biological aspect represented by the dreamer’s health. Following this point of view, at least in our observations, specific dream patterns may be ahead by months or years of the acute cardiac event as if the dream symbols reflect how the dreamer is behaving towards his/her health (concerning both lifestyle and choices/decisions in his/her existential context).

No studies have addressed the issue related to dream patterns in cardiac patients, and in psychosomatics in general.

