## 3. Endpoints and Outcome Measures

(A)Qualitative psychological endpoints:

The baseline and follow-up at one and five years of the psychological features in the four groups of subjects (TTS patients, AMI patients, BC women, and HS) as well as subjects classified according to psychotherapeutic treatment will be assessed by the per-protocol psychometric tests, the two enrollment questionnaires (see below), and the Six Drawing test (6DT).

The following qualitative psychological variables will be evaluated at enrollment and the one-year follow-up:Perception of body and emotions; qualitative analysis will be performed with two questionnaires, administered to all participants: (1) Enrollment body perception questionnaire (Supplementary Material S1); (2) One-year follow-up body perception questionnaire (Supplementary Material S2).Subject’s memory of last week, last month, last year, and past years’ dreams only at enrollment. A qualitative analysis will be performed with two questionnaires, administered to all participants: (1) Enrollment dream questionnaire (Supplementary Material S3); (2) One-year follow-up dream questionnaire (Supplementary Material S4).6DT patterns characteristics

(B)Medical endpoints

Based on the patients’ choice after enrollment, if the size of groups undergoing psychotherapy and those declining is sufficient to allow comparisons, the following medical endpoints will be assessed:-In AMI and TTS pts: the cumulative incidence of new cardiac events (i.e., MI, revascularization, life-threatening ventricular arrhythmias, recurrence of typical angina pectoris, stroke, and death all-cause), plus the occurrence of any clinically significant new medical disorder (active diseases requiring hospitalization or chronic medical therapy, or that cause a transient or permanent physical limitation), at the one and five-year follow-up in patients undergoing psychotherapy plus standard medical therapy and those on standard medical therapy only.-In BC patients: the incidence of breast cancer relapse, metastasis, or the occurrence of any clinically significant new medical disorder (that is an active disease requiring hospitalization or chronic medical therapy, or that cause a transient or permanent physical limitation), at the one and five-year follow-up in patients undergoing psychotherapy plus standard therapy and those on standard therapy only.-In all pts: new hospital admissions.

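### The one-year body perception and dream questionnaires cannot separate psychological benefit from practice or reporting effects when psychotherapy is compared with no psychotherapy

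*Protocol article*

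**What the plan says.** The Abstract lists the efficacy of the intervention on psychological as well as medical outcomes among the endpoints. Section 3(A) covers the four diagnostic groups "as well as subjects classified according to psychotherapeutic treatment will be assessed by the per-protocol psychometric tests, the two enrollment questionnaires" and the 6DT. It places the body perception questionnaire, the dream questionnaire and the 6DT at enrollment and one year.

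Section 3.1 states that "these two questionnaires will permit evaluation of qualitative changes during psychotherapy, compared to the control group". It adds that the open questions in both forms "have been elaborated based on the observations that emerged from the psychotherapeutic practice in the STEP IN AMI trial", and that their validity is being tested for the first time. It also says that dream material collected during therapy is entered on the form for patients who underwent psychotherapy.

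On the therapy, section 2.3 says: "This approach includes a thorough analysis of unconscious dynamics, mainly represented by body emotions and dream material". The Rationale for the Study Aims reports that in the earlier trial "there was an improvement of body/emotional perception during psychotherapeutic intervention with body relaxation training". Section 3.2.2 keeps that trial's session format and states the intended inference: "It will also be possible to evaluate if psychotherapy might result in an improvement in psychological patterns compared to medical therapy alone". It goes on to consider how such an improvement might carry over into medical prognosis.

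**The concern.** An outcome that compares a treated with an untreated group should be able to show no difference when the treatment does no good. That is doubtful when the treatment rehearses what the instrument asks about. A patient who has spent sessions attending to bodily sensations and recounting dreams may report more of both a year later, whether or not distress, anxiety or quality of life has changed. An untreated patient has met these topics in the study only when completing the forms.

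If such a shift is read as psychological improvement, and then as a possible route to better prognosis, part of the efficacy statement is circular. Self-selection into psychotherapy is a separate problem that affects every outcome here. The overlap between therapy and instrument would remain even if the two groups were identical at baseline.

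**Working it through.** The plan gives no figure on this point. Its only sample size calculation (55 AMI patients, 43% against 78%) concerns the earlier trial's composite endpoint and has no bearing on these instruments. The check therefore sets the statements side by side.

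**1. Are the instruments in the treated-versus-untreated comparison?** Yes. Section 3(A) classifies subjects by psychotherapy status and names both questionnaires, and section 3.1 states the comparison directly. The article also uses the term control group for the healthy subjects. However, section 3.2.2 compares each psychotherapy group with its own untreated group (AMI, TTS, BC) and gives the healthy subjects an independent follow-up after the initial comparison. I therefore read the comparator as the untreated patients. The point would hold on either reading, since the study gives neither comparator any sessions.

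**2. Does the therapy work on what is measured?**
- *Body perception.* The Rationale describes a missing perception of parts of the body as the adverse pattern. It describes guided attention to bodily sensations, in individual and group meetings, as part of the earlier therapy. The questionnaire asks about perception of body and emotions.
- *Dreams.* Section 2.3 makes dream material a main object of the therapy. The Rationale counts absence of dream recall among the patterns seen before infarction. The questionnaire asks what dreams the subject remembers, so practice in recalling dreams could register as recovery.
- *6DT.* Section 3.1 says it was defined by the same school and was used to guide therapy in the earlier trial. Nothing says that patients draw, or rework drawings, in sessions here.

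**3. Are the data gathered in the same way in both groups?** Not for dreams. Treated patients have session material added to the form (section 3.1), and untreated patients have no such source. Section 4 then takes the same school's manual as the initial reference for classifying dreams.

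**4. How large is the effect?** Exposure between enrollment and one year is at most 10 + 5 = 15 sessions in a psychotherapy group, against 0 in its comparison group. This applies to each of the three comparisons. A session count is not a bias estimate. No scoring rule, standard deviation or expected difference is given, so no range can be computed.

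For some dream features even the direction is open. The Rationale also lists distressing dreams and nightmares as adverse, and an extra source of dreams could raise their count in treated patients.

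**5. What is unaffected?** The enrollment comparisons between diagnoses precede therapy. The standard psychometric and quality-of-life scales at one and five years are not specific to this therapy. The medical endpoints are separate.

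**The case against.** The strongest reply is that changing body perception and dream patterns is what the therapy aims at, and measuring a therapy's target is ordinary practice. The study is described as a pilot, and the Discussion puts its main purpose at enrollment. Section 3.1 speaks of qualitative change and not of benefit. Section 3.2.2 names no instrument and makes between-group analysis conditional on balanced groups. The standard scales are already collected.

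Much of this stands, and it limits the point. Three stronger readings are tempting but unsupported:
- *That a difference is close to certain, or would show only that therapy was delivered.* Without scores or expected differences the documents cannot establish this. The questionnaire items are in supplementary material that is not shown, so the overlap is established for the constructs and not item by item.
- *That the 6DT is affected to the same degree.* Guiding the therapist in an earlier trial is not the same as patients practising the task in this one.
- *That the plan rests psychological efficacy on these instruments alone.* Section 3(A) lists them together with the standard psychometric tests.

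The reply does not remove the core. The Abstract lists psychological efficacy as an endpoint, and nothing in sections 3(A), 3.1 or 3.2.2 keeps the therapy-linked questionnaires out of that judgement. Section 2.3 itself asks that a psychotherapy improve global health before it is called efficacious, and altered dream reporting alone would not show that. The external committee in section 4 could limit rater bias if masked, but it could not undo practice effects or the extra dream source.

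**Conclusion.** The point holds for the body perception and dream questionnaires at one year, in all three comparisons of psychotherapy with none. Following the plan as written could lead practice or reporting effects to be read as psychological improvement. It is clearest for dreams, where overlap in content is joined by unequal data collection. It holds in a weaker form for the 6DT. Its size cannot be derived.

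The conclusion rests on two assumptions: that the therapy content resembles that of the earlier trial, whose session format is retained, and that the session dreams enter the one-year dream form. It should be corrected, but it does not undermine the enrollment comparisons, the standard scales or the medical endpoints.

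**What to change.** In sections 3(A) and 3.2.2, state the following:
- Conclusions on the psychological efficacy of the psychotherapy rest on the standard scales already given to all patients: BDI, STAI and STAXI-2, with the Self-evaluation test. The disease-specific quality-of-life scales are added within each diagnosis (MacNew for AMI and TTS; EORTC QLQ-C30 and QLQ-BR23 for BC).
- One-year differences between psychotherapy and comparison groups on the body perception and dream questionnaires, and with similar caution on the 6DT, are process or descriptive measures. They do not by themselves support a conclusion of efficacy.
- That comparison uses only dream data collected the same way in both groups. Session dreams may be kept, but are reported apart.

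The enrollment comparisons between diagnoses stay as they are. The cost is wording plus a rule that keeps session dreams separate; no new instrument or visit is needed. The sponsor gives up efficacy claims based on the therapy-specific instruments. The change does not deal with self-selection into psychotherapy, which affects the standard scales too.
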